## Abstract

Afatinib is an *ErbB* family blocker approved for the treatment of epidermal growth factor receptor mutation‐positive nonsmall‐cell lung cancer. A pivotal trial demonstrated significant clinical benefits with manageable toxicity of afatinib as a second‐line treatment option in squamous cell carcinoma of the lung (SCC) which led to approval in >60 countries. However, these results were derived from a controlled study conducted in selected patients and are not necessarily representative of the real‐world use of this drug. In addition, data on afatinib use after immunotherapy in this clinical setting are lacking. The aim of this study is to evaluate the treatment outcomes and safety of afatinib as a second‐ or later‐line treatment for SCC and to identify potential predictive biomarkers. As a real‐world observational study, 130 eligible patients with advanced SCC, who progressed after platinum‐based chemo‐ and immunotherapy, will be enrolled. Treatment outcomes and safety data will be collected for both the retrospective and prospective cohorts, and molecular profiling using tissue and plasma will be performed for the prospective cohort. The primary endpoint is time to treatment failure, and the secondary endpoints are objective response rate, progression‐free survival, overall survival, and safety. Comparison of clinical outcomes with respect to the different programmed death‐ligand 1 expression and molecular characteristics will also be carried out. This study will provide additional evidence on the usefulness of afatinib as a subsequent treatment, as well as feasible molecular biomarkers to predict its efficacy in this clinical setting.

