
Although ICIs, either used alone or in combination with chemotherapy, are recommended as first‐ and second‐line treatments in SCC, clinical data on afatinib use after both platinum‐based chemotherapy and ICI failure are lacking. To broaden our understanding of afatinib use in SCC, we aim to assess its efficacy and safety as a second‐ or later‐line treatment in real‐world clinical practice and to identify potential biomarkers using molecular profiling data. Our results could provide further support for the use of afatinib as a treatment option in patients who experience progression after both chemotherapy and immunotherapy. In addition, molecular biomarkers could help us predict response and select patients who will show favorable outcomes before afatinib use, which may facilitate “personalized medicine” in this clinical setting.

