## PATIENTS AND METHODS

### Study design

The SPACE study is a retrospective and prospective, observational, multicenter study. Figure 1 shows the flow chart for this study. Our aim is to evaluate the treatment outcomes and safety of afatinib in patients with advanced SCC who progressed after first‐line platinum‐based chemotherapy plus immunotherapy or platinum‐based chemotherapy followed by immunotherapy. We aim to recruit 130 patients, for retrospective and prospective cohorts of 30 and 100 patients, respectively, from four institutes in South Korea from January 2021 to December 2021. The observational period will be 1 year from the time of final registration. This is not a powered study. The minimum sample size has been set at 130 eligible patients to provide meaningful results.

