### Eligibility criteria

The inclusion criteria are as follows: (a) histologically confirmed as advanced, metastatic, or recurrent SCC; (b) history of first‐line platinum‐based doublet chemotherapy plus immunotherapy or first‐line platinum‐based chemotherapy followed by subsequent immunotherapy; (c) receiving afatinib as a second‐ or later‐line treatment; (d) age >18 years; and (e) provision of written informed consent. Patients who were treated with other EGFR‐tyrosine kinase inhibitors will be excluded.

Afatinib was approved by the Korean FDA in September 2018 for the treatment of SCC. Patients who had completed treatment with afatinib before the initiation of the study will be assigned to the retrospective cohort. Patients who will be on afatinib treatment by the day of initiation of the study or those who will start receiving this drug after the initiation of the study will be assigned to the prospective cohort. Written informed consent will be waived for patients in the retrospective cohort.

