## STATISTICAL ANALYSIS

All of the time‐to‐event data on treatment outcome parameters will be estimated using the Kaplan–Meier method. The median value and a two‐sided 95% CI will be described. Univariate and multivariate Cox regression analyses will be performed to estimate the potential clinical parameters or molecular subtypes associated with treatment outcomes.

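### With every patient on afatinib, marker associations with TTF, PFS and OS cannot be split into prognostic and predictive effects, so the predictive-biomarker aim and conclusion go beyond the design

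*Protocol article*

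**What the plan says.** **Claims.** The Abstract gives one aim of the study as "to identify potential predictive biomarkers". Its last sentence promises, with no hedge, "feasible molecular biomarkers to predict its efficacy in this clinical setting". The end of the Introduction states the intended use: "molecular biomarkers could help us predict response and select patients who will show favorable outcomes before afatinib use", and links this to personalised treatment.

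**Design.** Under Study design: "The SPACE study is a retrospective and prospective, observational, multicenter study", with targets "for retrospective and prospective cohorts of 30 and 100 patients, respectively". Under Eligibility criteria, one inclusion criterion is "receiving afatinib as a second‐ or later‐line treatment". The two cohorts differ in when afatinib was given, not in whether it was given. No group on another treatment is described.

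**Analysis.** Data collection plans subgroup analyses by PD-L1 level and genetic alteration, with sequencing in the prospective cohort only. Statistical Analysis says: "Univariate and multivariate Cox regression analyses will be performed to estimate the potential clinical parameters or molecular subtypes associated with treatment outcomes".

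**The concern.** A marker is predictive for a drug if the drug's effect, relative to some alternative, differs by marker status. Estimating that requires treatment to vary within marker groups. Here treatment is constant, so the only available contrast is marker-positive against marker-negative patients on the same drug. A difference may mean that the marker identifies patients who would do better on any treatment, that it identifies those in whom afatinib works better, or some mixture.

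Under the stated aim, an alteration or PD-L1 level that merely goes with slower disease could be read as predicting afatinib efficacy and taken forward as a basis for choosing patients. Patients without it might then be thought to gain less from the drug when their relative benefit is the same. The document does not say anywhere that the two effects cannot be separated. An analysis plan could not supply the missing contrast, because the limit lies in who is enrolled and not in the choice of model.

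**Working it through.** The plan gives no derived figure on this point, so there is nothing to reproduce. The check is on what the planned model can estimate.

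**1. Model.** Let T = 1 for afatinib and 0 for an alternative, and M = 1 for marker-positive. A hazard allowing both kinds of effect is

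h(t) = h0(t) · exp(aT + bM + cTM),

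where exp(a) is the afatinib effect in marker-negative patients, exp(b) the prognostic effect and exp(c) the predictive effect (interaction).

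**2. What is left when T = 1 for everyone.** The hazard becomes h0(t) · exp(a) · exp((b + c)M). The factor exp(a) is absorbed into the baseline. The Cox model estimates only b + c, that is, the product exp(b) · exp(c). Adjusting for clinical covariates does not change this, since treatment still does not vary.

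**3. Inputs for an illustration.** All come from the Introduction:
- PFS hazard ratio 0.62 for ErbB mutation-positive against mutation-negative disease, used as the within-afatinib value. The text does not make clear in which treatment arm or arms it was estimated, so it only sets a scale.
- PFS hazard ratio 0.82 for afatinib against erlotinib, taken as exp(a).

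**4. Results.** The afatinib effect in marker-positive patients is 0.82 × exp(c).

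| Scenario | exp(b) | exp(c) | Marker HR on afatinib | Marker HR on alternative | Afatinib HR, marker-positive | Afatinib HR, marker-negative |
|---|---|---|---|---|---|---|
| Purely prognostic | 0.62 | 1.00 | 0.62 | 0.62 | 0.82 | 0.82 |
| Equal mixture | √0.62 = 0.79 | 0.79 | 0.62 | 0.79 | 0.82 × 0.787 = 0.65 | 0.82 |
| Purely predictive | 1.00 | 0.62 | 0.62 | 1.00 | 0.82 × 0.62 = 0.51 | 0.82 |

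The study can observe only the fourth column, which is the same in every row. The columns that matter for selection differ.

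**5. Confirmation by simulation.** Exponential times were generated for 400,000 patients, with 21.6% marker-positive (the ErbB mutation figure in the Introduction), a median of 2.4 months and an assumed 1:1 comparator. The marker hazard ratio on afatinib was 0.62 in both pure scenarios. On the comparator it was 0.63 (prognostic) and 1.00 (predictive). The ratio of the two marker hazard ratios was 0.99 and 0.63. The afatinib effects were 0.81 against 0.82 (prognostic) and 0.51 against 0.82 (predictive). Only the comparator separates the cases.

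**6. The article's own example.** The Introduction reports two kinds of marker result from the earlier randomised comparison: outcome in ErbB-mutated against non-mutated disease, and outcome on afatinib against erlotinib when ErbB2 is mutated. The second needed a comparator. This study can produce only the first kind.

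**The case against.** The best defence is that the article is more modest than its aim suggests. The Statistical Analysis section speaks of association, Study design says the study is not powered, and no predictive test, decision rule or confirmatory hypothesis is fixed. The Abstract says potential, and the Introduction says could. Predicting response may mean tumour response, which is a planned endpoint and is less open to a purely prognostic explanation than survival-type outcomes. Any misuse of the results lies in a report not yet written.

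Much of this stands. The Statistical Analysis wording is correct, two of the three claims are hedged, and looking for candidate markers in such a cohort is legitimate. For these reasons the point is confined to TTF, PFS and OS. What does not stand is the Abstract's closing sentence, which carries no hedge, and the step to "select patients who will show favorable outcomes before afatinib use", which implies choosing who receives the drug.

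A reader might go further and infer any of the following, none of which the documents support:
- *The Cox analysis is mis-specified.* It is not. It claims only association.
- *The selection statement must be deleted.* Qualifying it is enough, given its hedge and the response endpoint.
- *The factors should be called prognostic instead.* By step 2 above, that label is as unidentifiable as predictive.
- *The sample size is in error.* The plan disclaims power, and the problem would be the same at any size.

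**Conclusion.** The point holds in this limited form: for TTF, PFS and OS, the design identifies only the combined marker association among afatinib-treated patients. The predictive-biomarker aim, the unhedged closing sentence of the Abstract and the patient-selection statement in the Introduction therefore claim more than the study can show.

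In the illustration, one observed hazard ratio of 0.62 is compatible with an afatinib effect in marker-positive patients anywhere from 0.82 (no basis for selection) to 0.51, against 0.82 in marker-negative patients. That range covers only markers whose prognostic and predictive effects do not oppose each other. It assumes proportional hazards and borrows the 0.62 and 0.82 from the Introduction. The non-identifiability itself depends on none of these numbers, only on all patients receiving afatinib.

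The endpoints, sample size and planned models are unaffected, and the descriptive primary objective stands. The change should be made because it alters what the study may conclude about markers.

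**What to change.** In the Abstract, restate the aim and the planned conclusion along these lines: *molecular and PD-L1 factors associated with outcome in afatinib-treated patients (prognostic and predictive effects not separable); hypothesis-generating for prediction*. In the Introduction, qualify the selection statement by saying that any use of such markers to choose patients would need confirmation in a comparative study with a marker-by-treatment contrast. Leave the Statistical Analysis sentence as it is.

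Do not label the factors prognostic. Do not try to recover a treatment-specific signal by comparing each patient's TTF on afatinib with TTF on the preceding line. All patients have had immunotherapy, which may be that line, so a marker that affects its duration would move the ratio with no afatinib effect. Preceding lines will also vary, since afatinib may be second- or later-line.

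The change is wording only, with no effect on recruitment, assays, data collection or models. The cost is a less ambitious claim.

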## INTRODUCTION

Squamous cell carcinoma of the lung (SCC) constitutes 30% of all lung cancers and is the second most common histological subtype of nonsmall‐cell lung cancer (NSCLC).^1^, ^2^ As with the majority of patients with lung cancer, approximately two‐thirds of patients with SCC are diagnosed at an advanced stage.^1^ While molecularly targeted therapy has revolutionized the treatment of adenocarcinoma with genetic alterations, including the epidermal growth factor receptor (EGFR) and anaplastic lymphoma kinase, treatment options for SCC are relatively limited compared to those of adenocarcinoma.^3^ Although platinum‐based chemotherapy has been used as a first‐line treatment, its clinical outcomes are still modest.^4^, ^5^

Recently, immune checkpoint inhibitors (ICIs), including pembrolizumab, nivolumab, atezolizumab, and the vascular endothelial growth factor receptor‐2 antibody ramucirumab (in combination with docetaxel), have been approved as new second‐line treatments for SCC.^5^, ^6^ Furthermore, pembrolizumab monotherapy for high programmed death‐ligand 1 (PD‐L1) expressors and taxane‐based chemotherapy combined with pembrolizumab regardless of PD‐L1 expression levels have been approved as novel first‐line treatments.^6^ However, overall clinical outcomes are still inferior compared to those for adenocarcinoma even with similar treatment strategies,^4^, ^7^, ^8^, ^9^ highlighting the unmet clinical need in this patient population.

SCCs are genetically complex and characterized by high mutation rates.^3^ Comprehensive molecular profiling has revealed that these cancers harbor numerous genomic and epigenomic alterations, with a reported mean of 360 exonic mutations, 165 rearrangements, and 323 segments of copy number alterations per tumor.^3^, ^10^ The Cancer Genome Atlas Project compared SCC tissue samples to normal pulmonary tissue to identify potential actionable mutations, and 11 common genomic abnormalities were observed, including those touching tumor protein 53, cyclin‐dependent kinase inhibitor 2A (*CDKN2A*), phosphatase and tensin homolog (*PTEN*), and *PIK3CA*.^10^ The genetic complexity of SCC is largely attributable to tobacco smoking, which compromises treatment success. With such a complex genetic landscape and associated high immunogenicity, this tumor type has been targeted for immunotherapy and chemotherapy. However, the development of targeted agents has, so far, represented a significant challenge.^11^

Studies have suggested that SCC is strongly dependent on the *ErbB* family pathway; *ErbB1* (*EGFR*) is overexpressed in about 70% of SCCs, whereas *ErbB2* and *3* are overexpressed in 20–30% of cases. In addition, gene copy‐number alterations of *EGFR* were found in 7–10% of SCCs.^12^, ^13^, ^14^, ^15^, ^16^ Although *EGFR* mutations were less common, 21.6% of SCC patients had at least one *ErbB* mutation.^16^, ^17^, ^18^, ^19^ These data provide a biological rationale for *ErbB*‐targeted therapy in this histologic subtype. Afatinib, an irreversible *ErbB* inhibitor, can inactivate aberrant *ErbB*‐dependent signaling pathways and has been postulated to be effective in treating SCC.^20^, ^21^ In the LUX‐Lung 8 trial, afatinib (40 mg/day, *n* = 398) was compared to erlotinib (150 mg/day, *n* = 397) in stage IIIB/IV SCC patients who had received at least four cycles of chemotherapy with platinum doublet agents.^22^ Afatinib was better in terms of both progression‐free survival (PFS) and overall survival (OS) (PFS 2.4 vs. 1.9 months, hazard ratio [HR] 0.82, 95% confidence interval [CI] 0.68–1.00, *p* = 0.041; OS 7.9 vs. 6.8 months, HR 0.81, 95% CI 0.69–0.95, *p* = 0.0077). Although a 1.1‐month difference in OS in a head‐to‐head comparison can be clinically questionable, especially considering its translation into routine clinical practice, the survival rate at 12 (36% vs. 28%, *p* = 0.016) and 18 months (22% vs. 14%, *p* = 0.013) was significantly higher with afatinib, suggesting a prolonged benefit of this drug.^22^ Furthermore, the safety profiles were similar in both groups. Based on the significant improvements in PFS and OS along with a manageable safety profile, in April 2016 the US Food & Drug Administration (FDA) approved afatinib as a new oral treatment option for SCC that progressed after platinum‐based chemotherapy. A subsequent analysis, which assessed the association between clinical outcomes and *ErbB* family member gene alterations, showed that PFS (median 4.9 vs. 3.0 months, HR 0.62, 95% CI 0.37–1.02, *p* = 0.06) and OS (median 10.6 vs. 8.1 months, HR 0.75, 95% CI 0.47–1.17, *p* = 0.21) was numerically longer among those with *ErbB* mutation‐positive disease than among those without.^16^ Furthermore, the presence of *ErbB2* mutations was associated with more favorable PFS and OS following afatinib than erlotinib treatment.^16^ These data suggest that specific molecular characteristics can be biomarkers for afatinib treatment success in SCC, and genomic profiling may help identify patients with SCC who may derive additional benefits from treatment with this drug.

Although ICIs, either used alone or in combination with chemotherapy, are recommended as first‐ and second‐line treatments in SCC, clinical data on afatinib use after both platinum‐based chemotherapy and ICI failure are lacking. To broaden our understanding of afatinib use in SCC, we aim to assess its efficacy and safety as a second‐ or later‐line treatment in real‐world clinical practice and to identify potential biomarkers using molecular profiling data. Our results could provide further support for the use of afatinib as a treatment option in patients who experience progression after both chemotherapy and immunotherapy. In addition, molecular biomarkers could help us predict response and select patients who will show favorable outcomes before afatinib use, which may facilitate “personalized medicine” in this clinical setting.

## PATIENTS AND METHODS

### Study design

The SPACE study is a retrospective and prospective, observational, multicenter study. Figure 1 shows the flow chart for this study. Our aim is to evaluate the treatment outcomes and safety of afatinib in patients with advanced SCC who progressed after first‐line platinum‐based chemotherapy plus immunotherapy or platinum‐based chemotherapy followed by immunotherapy. We aim to recruit 130 patients, for retrospective and prospective cohorts of 30 and 100 patients, respectively, from four institutes in South Korea from January 2021 to December 2021. The observational period will be 1 year from the time of final registration. This is not a powered study. The minimum sample size has been set at 130 eligible patients to provide meaningful results.

**FIGURE 1 tca13880-fig-0001:**
[figure not shown]
Study flowchart. DCR, disease control rate; DoR, duration of response; NGS, next‐generation sequencing; ORR, objective response rate; OS, overall survival; PD‐(L) 1, programmed death‐(ligand) 1; PFS, progression‐free survival; SCC, squamous cell carcinoma of the lung; TTF, time to treatment failure

The primary endpoint of this study is the time to treatment failure (TTF), defined as the time from the start of afatinib treatment to the time of treatment discontinuation for any reason, including disease progression, treatment toxicity, and death. The secondary endpoints are the objective response rate (ORR), duration of response (DoR), disease control rate (DCR), PFS, OS, and safety profiles. In addition to these, the difference in treatment outcome parameters with respect to PD‐L1 expression and genetic alterations will be analyzed. This protocol has been approved by the Medical Ethics Committee of the Kyung Hee University Medical Center, Seoul, South Korea, and all participating institutes. As this study involves human participants, all procedures will be performed in accordance with the ethical standards of the Institutional and National Research Committee, and the 1964 Declaration of Helsinki and its later amendments or comparable ethical standards. This study is subject to the supervision and management of the ethics committees of all participating institutes. This study is registered in the Clinical Research Information Service (CRIS, https://cris.nih.go.kr, registration number KCT0005712), the official registration site for clinical trials powered by the Korea Disease Control and Prevention Agency.

### Eligibility criteria

The inclusion criteria are as follows: (a) histologically confirmed as advanced, metastatic, or recurrent SCC; (b) history of first‐line platinum‐based doublet chemotherapy plus immunotherapy or first‐line platinum‐based chemotherapy followed by subsequent immunotherapy; (c) receiving afatinib as a second‐ or later‐line treatment; (d) age >18 years; and (e) provision of written informed consent. Patients who were treated with other EGFR‐tyrosine kinase inhibitors will be excluded.

Afatinib was approved by the Korean FDA in September 2018 for the treatment of SCC. Patients who had completed treatment with afatinib before the initiation of the study will be assigned to the retrospective cohort. Patients who will be on afatinib treatment by the day of initiation of the study or those who will start receiving this drug after the initiation of the study will be assigned to the prospective cohort. Written informed consent will be waived for patients in the retrospective cohort.

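### Cohorts are assigned by treatment status at study initiation, so the primary outcome decides the cohort and TTF is truncated in opposite directions in the two cohorts

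*Protocol article*

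**What the plan says.** All references are to the protocol article.

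- **Primary endpoint** (Study design, text after Figure 1): TTF is "defined as the time from the start of afatinib treatment to the time of treatment discontinuation for any reason".
- **Retrospective cohort** (Eligibility criteria): "Patients who had completed treatment with afatinib before the initiation of the study will be assigned to the retrospective cohort".
- **Prospective cohort** (same paragraph): patients on afatinib on the day the study starts, "or those who will start receiving this drug after the initiation of the study will be assigned to the prospective cohort".
- **Size** (Study design): "We aim to recruit 130 patients, for retrospective and prospective cohorts of 30 and 100 patients, respectively", from four institutes during 2021. The section adds "This is not a powered study" and "The minimum sample size has been set at 130 eligible patients to provide meaningful results". It gives no rule for which completers make up the 30.
- **Earliest use** (Eligibility criteria): "Afatinib was approved by the Korean FDA in September 2018 for the treatment of SCC".
- **Analysis** (Statistical analysis): Kaplan–Meier medians with two-sided 95% confidence intervals, and univariate and multivariate Cox models. The section does not say whether the cohorts are pooled.

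**The concern.** Take two patients who start afatinib on the same day in 2020. One stops before the study begins and is retrospective. The other is still on drug and is prospective. Only the value of the primary endpoint separates them.

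Two distortions follow. In the retrospective cohort every patient has had the event, and no TTF can exceed the gap between that patient's start and study initiation. This is right truncation. In the prospective cohort, patients already on drug are there because they lasted long enough to be on drug at initiation, yet their TTF runs from the earlier start. This is left truncation, and an ordinary Kaplan–Meier estimate credits them with time during which they could not have been observed to fail.

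Median TTF is the main result of this study. A difference between the cohorts would be partly produced by their definitions, and a pooled median would depend on the mix of patient types as well as on the drug.

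**Working it through.** **Plan's own figure.** 30 + 100 = 130, as stated. There is no power or precision calculation to reproduce.

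**Inputs.** September 2018 (approval) to January 2021 gives a look-back of W = 28 months; initiation in January 2021 is an assumption. Recruitment lasts A = 12 months. The documents give no expected TTF, so the true median m is assumed. The range 2.4 to 4.9 months borrows two median PFS values from the Introduction: 2.4 for afatinib in the cited randomised trial, and 4.9 for its *ErbB*-mutation-positive subgroup. The middle value is 3.0. TTF is taken as exponential with λ = ln 2 / m, and starts as uniform over time.

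**Retrospective cohort.** A patient who started u months before initiation is a completer only if TTF < u. The density of observed TTF is therefore proportional to f(t)(W − t), with cumulative weight

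G(t) = W(1 − e^(−λt)) − [(1 − e^(−λt))/λ − t·e^(−λt)].

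The median solves G(t) = G(W)/2. For m = 3.0, λ = 0.2310, G(28) = 23.68 and half of that is 11.84, reached at t = 2.52 months.

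| Assumed true median | Retrospective median, W = 28 | Bias |
|---|---|---|
| 2.4 | 2.09 | −13% |
| 3.0 | 2.52 | −16% |
| 4.9 | 3.61 | −26% |

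If eligible starts fall only in the last 12 months, the m = 3.0 result is 1.91 months (−36%).

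**Prospective cohort, m = 3.0.** Patients on drug at initiation amount to (1 − e^(−λW))/λ = 4.32 months' worth of starts, against 12 for new starters. Their share is 4.32/16.32 = 26.5%. Their TTF density is proportional to f(t)·min(t, W), with median 7.25 months. Without delayed entry the whole prospective cohort has median 3.93 months (+31%).

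**Pooled 30 + 100, m = 3.0.** Write F_R, F_P and F_N for the TTF distributions of completers, patients already on drug and new starters.

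- *Patients on drug enter in proportion.* At t = 3.54, F_R = 0.624, F_P = 0.198 and F_N = 0.559. The prospective value is 0.265 × 0.198 + 0.735 × 0.559 = 0.463. Pooled: (30 × 0.624 + 100 × 0.463)/130 = 0.50. The median is 3.54 months (+18%).
- *None enter.* At t = 2.88, F_R = 0.548 and F_N = 0.486, and (30 × 0.548 + 100 × 0.486)/130 = 0.50. The median is 2.88 months (−4%).
- *Everyone is enumerated, with no targets.* The weights are 23.68 + 4.32 + 12 = 40 months of starts, and the median is 3.00. The two truncations cancel exactly.

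**Sensitivity.** A simulation used exponential, Weibull (shape 0.8) and lognormal (sigma 1) TTF, true medians of 2 to 6 months, and uniform or linearly rising starts. The retrospective median was too low in every case: −10% to −44% with uniform starts and −17% to −57% with rising starts. The pooled median, with proportional entry, was too high in all 24 cases: +13% to +36% with uniform starts and +3% to +10% with rising starts.

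**The case against.** Three stronger readings are tempting, and the document supports none of them.

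- *The retrospective cohort is capped at 30.* Study design gives 30 as a recruitment aim and 130 as a minimum. No cap is stated.
- *The study's TTF as a whole is biased downward.* That holds for the retrospective cohort read alone. A pooled estimate is too high under most assumptions tried, and slightly too low only when few or no patients already on drug enter.
- *Completers are sampled at a known low rate.* No start rate is given. Across the simulated scenarios 37 to 169 completers exist per 100 prospective patients, so 30 could be most of them or a small part.

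Other objections have weight. The article does not say that the cohorts will be pooled. Separate reporting, stratification and delayed entry are ordinary content for an analysis plan that is not shown. Data collection requires plasma taken before afatinib, which may limit how many patients already on drug contribute fully, although it is not an entry criterion. The study is not powered. With 30 patients, an exponential approximation to the Kaplan–Meier interval for the median spans a factor of exp(1.96/(0.693 × √30)) = 1.7 either way, wider than a 16% bias.

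What remains is the entry rule, which the article itself fixes. An analysis plan can handle patients already on drug by delayed entry. It cannot recover long durations from a cohort that excludes them by definition. Nor does lack of power excuse bias, which would not shrink with more patients.

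**Conclusion.** The point holds in this form. Assignment by treatment status right-truncates the retrospective cohort and left-truncates part of the prospective cohort. The downward direction in the retrospective cohort follows from the rule and does not depend on the assumed distribution. Its size, about −13% to −26%, rests on assumed true medians of 2.4 to 4.9 months, exponential TTF, uniform starts and a 28-month look-back. It is larger if eligible starts are concentrated shortly before initiation.

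For a pooled estimate the document fixes neither direction nor size. At an assumed true median of 3.0 months it runs from about +18% with proportional entry of patients already on drug to about −4% with none. The defect is this dependence on an uncontrolled mix.

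**What to change.** **Preferred.** Define both cohorts by afatinib start date.

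- *Retrospective:* all consecutive patients at the four institutes who started before study initiation, or a consecutive sample chosen by start date, whether or not they had stopped. Those still on drug are censored, or followed under the applicable consent.
- *Prospective:* patients starting on or after initiation.

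On the assumptions above (m = 3.0), this returns a pooled median of 3.00 months. Both definitions must change. Closing the retrospective start window 12 months before initiation, while the prospective cohort still admits patients already on drug, left the simulated pooled median at 3.63 months.

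**If status-based assignment must stay.** Report the completers' TTF separately as descriptive and keep it out of the primary estimate. Use delayed-entry (left-truncated) Kaplan–Meier and Cox for patients on drug at initiation. Stratify any pooled Cox model by cohort.

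**Cost.** The preferred change amends the eligibility paragraph and needs a consecutive list of starters at each institute. Some on-treatment patients move to the retrospective cohort. That affects consent, which is waived there at present, and who receives molecular profiling, which is planned for the prospective cohort only. The ethics committees would need to agree how these patients are handled. The total of 130 can stay. The fallback changes only the analysis and reporting.
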